#### Strategies to improve adherence to interventions {11c}

Not applicable. The experimental intervention is performed in a single session, so it is not necessary to develop techniques to improve adherence to interventions.

#### Relevant concomitant care permitted or prohibited during the trial {11d}

Not applicable. The experimental intervention is performed in a single session, so it is not possible for the participant to receive concomitant cares during the trial.

#### Provisions for post-trial care {30}

No adverse effects are expected after the experimental session. However, if after the phase of negative emotional induction, the intervention aimed at their emotional recovery was not effective, the psychologist responsible for the session, using the appropriate psychological techniques, will be responsible for the individual having recovered the emotional state previous to the start of the experimental session.

### Outcomes {12}

Participants will first complete a sociodemographic questionnaire to collect data on the following variables: age, sex, educational level, current occupation, marital status relationship status, health problems, regular medication and self-perceived health status. Additionally, participants will be asked to complete a series of screening questionnaires.

#### Screening measures

##### Test Your Memory (TYM [83], Spanish adaptation [84])

The TYM is a cognitive screening test to detect Alzheimer’s disease and mild cognitive impairment. It consists of a set of 10 tasks, with a possible total score of 50 points. The following abilities are measured: orientation, ability to copy a sentence, semantic information, calculation, verbal fluency, similarities, confrontation naming and perception. The help required is scored on a 0–5 range, where 5 is no assistance at all. The higher the score obtained, the better is the performance. The cut off for cognitive impairment is 40 or below and 36 or below for dementia. The Spanish version has demonstrated adequate psychometric properties (*α* = .86) [84].

##### Patient-Reported Outcomes Measurement Information System-D (PROMIS®-Depression 4ª, short form) [85]

This version includes four items to measure a participant’s negative affect in the past 7 days, with five response options ranging from 1 = never, to 5 = always, where the higher the score, the greater is the negative affect. The test forms part of PROMIS-29, and total scores range between 4 and 20, where the highest scores correspond to more serious depressive symptoms [89]. The cut off is set at 11 points (http://www.helathmeasures.net). Indices of reliability for this version are excellent (*α* = .96).

##### Patient-Reported Outcomes Measurement Information System-A (PROMIS®-Anxiety 4a, short form) [85]

This version includes four items to measure symptoms of anxiety in the past 7 days with five response options ranging from 1 = never, to 5 = always, where the higher the score, the higher is the anxiety. It forms part of PROMIS-29, and total scores range between 4 and 20, where the highest scores correspond to the most severe symptoms of anxiety [89]. The cut off is set at 11 points (http://www.healthmeasures.net). Indices of reliability for this version are excellent (*α* = .96).

#### Mood state measures

##### Positive and Negative Affect Schedule (PANAS) [88]

This scale is composed of two 10-item subscales that measure the primary dimensions of mood state (positive affect and negative affect). The items describe adjectives associated with common feelings and emotions and are scored on a 5-point Likert-type scale ranging from 1 (very slightly or not at all) to 5 (extremely). The test provides separate scores for the two types of affect, and an affective balance score can be obtained by subtracting the negative affect score from that for positive affect [90], meaning that the higher the score, the greater is the predominance of positive affect. The validated version for Spanish population [91] has obtained alpha coefficients between .87 and .91.

#### Measurement of emotional experience in the experiments

##### Self-Assessment Manikin (SAM) [92]

This test measures five sub-dimensions (5 figures per dimension): (a) affective valence, pleasure or hedonism (SAM-Val), with manikins that range from smiling and happy to frowning and unhappy; (b) arousal or activation (SAM-Act), ranging from a wide-eyed figure to a sleepy one; and (c) dominance or controlled emotion (SAM-Dom), where the figures range from a small manikin indicating minimum control to a large, impassive figure. As the instrument requires no use of language, it is free of cultural influences and is thus adequate for use in different countries and cultures.

#### Control questions

##### Control questions following negative mood induction

To measure the participant’s level of immersion in the film clip used for negative mood induction, the following questions are used: (1) On a scale from 0 to 9, indicate your level of concentration while watching the film clip (0 = no concentration; 9 = total concentration), and (2) on a scale from 0 to 9, indicate to what degree you surrendered to the feelings generated by the film clip (0 = I did not surrender at all to the feelings in the film clip; 9 = I surrendered totally to the feelings in the film clip).

##### Control questions following exposure to the pictures/photographs

To assess the extent to which the participant felt involved in viewing the images chosen to elicit positive affect, the following questions are included: (1) On a scale from 0 to 9, indicate your level of concentration when recalling the event (0 = total lack of concentration; 9 = total concentration), and (2) on a scale from 0 to 9, indicate to what degree you were able to relive the positive emotions you felt at the moment of the event (0 = I was unable to relive the emotions; 9 = I was able to relive the emotions completely).

#### Devices used to acquire physiological signals and behavioural data

##### Brain Computer Interface (BCI)

BCI systems are able to detect, process and respond to affective states by means of physiological signals [93] and the analysis of frequency bands associated with such emotional states. EEG data will be obtained wirelessly using the EMOTIV Epoc+ (http://www.emotiv.com/epoc), which is formed by 14 electrodes, divided into sensors and two reference electrodes placed across both hemispheres. The electrodes are labelled according to the International 10-120 positioning system (AF3, F7, F3, FC5, T7, P7, O1, O2, P8, T8, FC6, F4, F8, AF4 and the reference electrodes P3 and P4).

##### Empatica E4

This device records heart rate and electrodermal activity signals (http://www.empatica.com/en-eu/research/e4/). It is a wireless device able to measure variables such as heart rate variability, interbeat interval, electrodermal activity, acceleration and skin temperature (HRV, IBI, EDA, ACC, TMP, respectively). It is one of the most efficient devices in the field and is certified by the US Food and Drugs Administration for medical use.

##### Software E-PRIME 3.0

This system allows psychological experiments to be designed, generated and reproduced and also records the experimental data and enables the data to be edited and analysed. It can play films and videos, digitally record participants’ sonic responses and can also be integrated with other equipment, such as EEG devices. It will be used to design the experimental task and collect and analyse the subjective data.

### Participant timeline {13}

Participant recruitment is expected to begin in October 2020 and continue for 2 months. Nevertheless, if the minimum number of participants in each experimental group is not reached in early December, the recruitment period will be extended until the required minimum is reached. In this phase, those who agree to participate will complete the screening questionnaires.

The pre-experimental and experimental phases will take place 7–21 days after randomization. Both phases will take place on the same day. In the pre-experimental phase, participants will select the images to be displayed in the experimental task according to the group to which they are assigned (low, medium or high personal relevance). Finally, in the experimental phase, they will complete the mood questionnaires and the experimental task.

**Table Tabb:** 

Activity/assessment	Approximate time to complete	TIME			
		− 1	0	1	
		Screening phase	Randomization	Pre-experimental phase	Experimental phase
Informed consent	5 min	X			
Test Your Memory	5 min	X			
PROMIS-Depression	5 min	X			
PROMIS-Anxiety	5 min	X			
Demographic questionnaire	10 min	X			
Assessment of inclusion criteria		N/A	X		
Randomization		N/A	X		
Selection of images for emotional recovery	25 min			X	
PANAS pre-emotional induction	5 min				X
Experimental task and questions about emotional experience during the task	25 min				X
PANAS post-emotional induction	5 min				X
PANAS post-emotional recovery	5 min				X

### Sample size {14}

This study requires a sample of 120 participants aged 65 or older (divided into three groups of 40) without cognitive impairment or major depressive disorder, and 120 young adults aged between 18 and 35 (divided into three groups of 40) with no major depressive disorder.

To calculate the sample size, we used GPower version 3.1., considering the following parameters: a 95% confidence interval (*p* < .05), an estimated power of 95%, a predicted medium effect size of 0.06 (partial eta squared; Cohen [94]), 6 repeated measures (6 pictures), an expected correlation between of .80 and 6 experimental groups (3 types of pictures × 2 age groups).

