#### Criteria for discontinuing or modifying allocated interventions {11b}

Not applicable. The interventions will not be modified. Participants may leave the trial at any time if they wish. Participants who do not complete the entire trial will be excluded from the study.

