## Statistical methods

### Statistical methods for primary and secondary outcomes {20a}

#### Statistical analysis of the subjective variables

All analyses will be conducted using SPSS24.0 software. Firstly, ANOVAs and chi-square tests will be conducted to determine whether significant differences exist between the different intervention groups for the variables collected (PROMIS and PANAS scales) in the first assessment phase (Time 1) and for the level of immersion when viewing the film clip during the negative mood induction. If differences between groups are found in any of these variables, the variables with statistically significant differences will be included as covariate variables in the following ANOVAs. Secondly, to assess the impact of personal relevance of the images in emotional recovery, a repeated-measures ANOVA and post hoc Bonferroni tests will be performed in a mixed design with type of image (low, medium and high personal relevance groups) and group (young and older) as between-subjects variables and time (pre-test—Time 1—, post-negative emotional induction—Time 2—and post-positive emotional induction—Time 3) as within-subject variables. Finally, to assess the sense of reliving for the three groups of images, a repeated-measures ANOVA and post hoc Bonferroni tests will be performed in a mixed design with type of image (low, medium and high personal relevance groups) and group (young and older) as between-subjects variables and (average score of concentration level recalling the events and average score of the degree of reliving the positive emotions of the remembered events) as within-subject variables.

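### The sample size is calculated for six repeated pictures, a factor no planned analysis contains, and its stated inputs do not return 240; the planned tests are not thereby shown to be underpowered

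*Protocol article*

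**What the plan says.** Sample size {14} asks for 120 older and 120 young adults, each split into three groups of 40. It cites G*Power 3.1 with a .05 significance level, 95% power, a medium effect of .06 as partial eta-squared, and "6 repeated measures (6 pictures), an expected correlation between of .80 and 6 experimental groups". It does not name the F-test or the effect that was powered.

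The planned analyses are these:
- **PANAS** (Statistical analysis of the subjective variables): a mixed ANOVA with image type and age group between subjects and "time (pre-test—Time 1—, post-negative emotional induction—Time 2—and post-positive emotional induction—Time 3) as within-subject variables".
- **Reliving** (same section): a mixed ANOVA on two ratings, concentration and reliving, each averaged over the pictures.
- **Skin conductance level and heart rate** (Processing and statistical analysis of objective variables): the same three times within subjects.
- **EEG** (EEG signal): spectra averaged across event types, then a group by time ANOVA.

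On losses, Criteria for discontinuing or modifying allocated interventions {11b} states: "Participants who do not complete the entire trial will be excluded from the study". The sample size section makes no allowance for this.

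**The concern.** A power statement should describe a test that will be carried out. Here the within-subject structure (six pictures, correlation .80) matches none of the four planned ANOVA families. PANAS is completed only three times in the session, so it cannot supply six measures.

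The section also names no F-test. With these inputs the required total runs from 18 to 264 under the default effect-size option, depending on the test, so a reader cannot tell what 240 is meant to achieve. This paragraph is the only stated justification for the number of people enrolled and put through a negative mood induction.

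**Working it through.** **Inputs from Sample size {14}.** Alpha = .05; power = .95; partial eta-squared = .06; m = 6 measures; rho = .80; k = 6 groups; N = 240.

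f² = .06/.94 = .0638, so f = .2526.

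**Step 1: try to reproduce 240.** The noncentral F distribution is used, with sphericity assumed. Totals are rounded up to a multiple of six.

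- *Between groups.* λ = f²·N·m/[1 + (m−1)rho], df = 5 and N−6. At N = 240, λ = .0638 × 240 × 6/5 = 18.38, df 5 and 234, power 92.6%. N = 264 is needed for 95%.
- *Within.* λ = f²·N·m/(1−rho), df = 5 and 5(N−6). N = 18.
- *Group by measure interaction.* Same λ, df = 25 and 5(N−6). N = 24.
- *Interaction, SPSS effect-size option.* λ = f²(N−6)(m−1). At N = 114, λ = .0638 × 108 × 5 = 34.5, df 25 and 540, power 95.0%. So N = 114.
- *Other SPSS-option tests.* Within, N = 72; between groups (5 df), N = 324.
- *Other variants.* The Cohen effect-size option gives 66 (within) and 114 (interaction). The default interaction at lower-bound epsilon gives 58. Taking f = .25 in the between-groups test gives 270.

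None returns 240.

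**Step 2: what would return it.** The 5-df between-groups test with rho = .70 in place of .80 has λ = .0638 × 240 × 6/4.5 = 20.4 and 95.2% power at 240, and its balanced total is exactly 240. A plain 3 × 2 ANOVA without repeated measures (2 df) needs 246. A misreported correlation or test is therefore possible, but the article does not say so.

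**Step 3: power of the planned three-time ANOVA at 240.** Here m = 3 and k = 6, with partial eta-squared .06.

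- *Image type × time* (2 × 2 = 4 df). SPSS option: λ = .0638 × 234 × 2 = 29.9, df 4 and 468, power 99.7%. Default with rho = .80: λ = .0638 × 240 × 3/.2 = 229.8, power over 99.9%.
- *Image type × age × time* also has 2 × 1 × 2 = 4 df, so the same figures apply.
- *Image type main effect* (2 df). Default with rho = .80: λ = .0638 × 240 × 3/2.6 = 17.7, df 2 and 234, power 97.0%. This depends on the correlation, for which the article gives no value across times: 99.3% at rho = .50, 98.0% at .70, 95.9% at .90. Under the SPSS option, λ = .0638 × 234 = 14.9 and power is 94.0%.

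**Step 4: excluding non-completers.** The article gives no loss rate, so these rates are assumptions.

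| Assumed loss | N | Image × time (SPSS option) | Image main effect (default, rho .80) |
|---|---|---|---|
| 5% | 228 | 99.5% | 96.3% |
| 10% | 216 | 99.3% | 95.3% |
| 15% | 204 | 98.9% | 94.1% |

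**Step 5: older adults alone** (N = 120, k = 3, three times). Image × time has about 88% under the SPSS option and almost 100% under the default. The 2-df image main effect has about 75% (default, rho .80).

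**The case against.** The strongest reply is that nothing is at risk. The trial is labelled exploratory under Trial design {8}, the planned tests are well powered at 240, and one wrong input could explain the mismatch. The first two points stand, and they rule out a stronger reading. A reader might infer from the 264 that the trial is too small. However, the 264 belongs to a 5-df comparison of all six cells at once, whereas the plan separates image type from age. A reader might also infer that no test reaches 95% at 240. In fact the within and interaction tests do, under either effect-size option.

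A reader might further infer a shortfall in older adults, whom the Objectives {7} single out. A stand-alone 2-df comparison at Time 3 in 120 people would have only 68.5% power. But no Time-3-only test is planned, age is a factor in the PANAS and reliving models, and Methods for additional analyses {20b} foresees no subgroup analyses.

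On losses, Participant timeline {13} and Recruitment {15} extend recruitment until a minimum per group is reached, and the experiment is a single session. This weakens the attrition point without removing it. The session follows randomization by 7 to 21 days, and the article does not say that the minimum counts completers.

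What the reply does not answer is that the published calculation cannot be reproduced and describes a design the trial does not analyse.

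**Conclusion.** The point holds as an error in the sample size justification. The calculation and the analyses appear in the same article and disagree, so this is not detail left to an analysis plan. The documents do not support a claim that 240 is inadequate for the planned tests. The one clear shortfall against 95% is the unplanned six-cell comparison. The image main effect sits close to 95% and falls on either side of it according to the effect-size convention.

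These conclusions rest on the protocol's own effect size, on sphericity and, for the default-option figures, on carrying the .80 correlation from pictures over to times.

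**What to change.** Keep 240 and rewrite the second paragraph of Sample size {14}:

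- Remove the six-picture repeated measure. Base the calculation on the mixed ANOVA planned for the subjective variables, with three time points.
- Name the powered effect (image type × time), its 4 df, the assumed correlation between times, and whether partial eta-squared is entered under the G*Power default or the SPSS option.
- Report the resulting power at 240, with the image main effect alongside.
- Check the saved G*Power run and correct whichever input or test was misreported.
- State how excluding non-completers lowers these figures, and whether the recruitment minimum counts completers.
- If any separate claim for older adults is intended, give it its own lower power from Step 5.

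The cost is one rewritten paragraph, with no extra participants and no change to the analyses.

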### Recruitment {15}

People interested in participating in this study will be provided with a detailed information sheet supplemented with a verbal explanation of the study procedure. If the participants agree with this information, the screening questionnaires will be completed. The research psychologists will obtain the informed written consent of each participant prior to the screening phase. The questionnaires in this phase will include a complete sociodemographic history, a screening test to assess the presence of cognitive impairment and scales to measure anxiety and depression symptoms. Of these individuals, all participants meeting the inclusion criteria will be recruited for the study. Recruitment will continue until the minimum number of participants in each group is reached.

### Assignment of interventions: allocation

#### Sequence generation {16a}

The online software Randomizer version 3.0 [95] will be used to randomly assign 40 participants to each of the three experimental conditions within each group (young and older adults). The random assignment will be conducted by a third party in order to ensure the researcher remains blind to the study.

#### Concealment mechanism {16b}

Participants will be randomly assigned to one of three groups (high, medium and low personal relevance images) with a 1:1:1 allocation as per the online software Randomizer version 3.0 [95]. Allocation concealment will be ensured as the randomization code will not be released until the participant has been recruited into the study, which takes place after all baseline measurements have been completed and after verifying that the inclusion criteria for participation are met and that informed consent has been provided.

#### Implementation {16c}

All patients who give consent for participation and meet the inclusion criteria will be randomized.

The random assignment of participants will be conducted by a member of the Psychology Department blinded to the objectives of the study. This staff member will send a third research psychologist a list with the random assignation of each participant to each intervention group. This psychologist will not be involved in the recruitment of participants or in assessing the outcomes of the study. The psychologists responsible for participant recruitment will not be allowed to receive information about group allocation.

Throughout the study, the randomization will be conducted by the same member of the Psychology Department in order to keep the data management and the statistician blind to the study condition. Thus, randomization will be conducted without any influence from the researchers involved in the study.

### Assignment of interventions: blinding

#### Who will be blinded {17a}

The psychologists responsible for participant recruitment will be blinded to the information about group allocation. Due to the nature of the intervention, neither participants nor psychologists responsible for the experimental phase can be blinded for the allocation, but the psychologist will be trained to reduce her influence on the participants as much as possible. To this end, she will be provided with clear steps and norms to follow during the experimental intervention.

#### Procedure for unblinding if needed {17b}

Unblinding should not be necessary in this study.

## Data collection and management

### Plans for assessment and collection of outcomes {18a}

Each psychologist participating in the data collection will be trained in the study requirements and the steps and specific norms to follow while the questionnaires and experimental tasks are administered.

A detailed description of the study instruments and their validity can be found in the outcomes section. The informed consent form and sociodemographic questionnaire are included in Additional files 1 and 2, respectively.

### Plans to promote participant retention and complete follow-up {18b}

Not applicable. The experimental intervention is performed in a single session, so it is not necessary to develop techniques to promote participant retention and complete follow-up.

### Data management {19}

Data from the screening phase will be entered and kept in a SPSS file by the research psychologists responsible for the data collection in this phase.

In the experimental phase, subjective questionnaires will be answered using e-prime software. This data will be added to another SPSS file. The same procedure will be conducted with the objective measures (heart rate variability, electrodermal activity and EEG), once these signals have been processed. All participants will receive the same identification in all SPSS files (screening, subjective measures and objective measures).

The psychologists responsible for the data analysis will merge the SPSS files to create a single SPSS file including all the data.

Participant files will be stored in numerical order in a secure and accessible place and manner. These files will be held in storage for a period of 3 years after completion of the study.

